### Methods for additional analyses (e.g. subgroup analyses) {20b}

To test whether effects observed in the analyses of the primary outcome depend on the severity of CUD, affect, and stress, the correlations between those measures are assessed. Post-hoc tests are adequately corrected for multiple comparisons.

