#### Ketamine’s effect on glutamate signalling

Ketamine, an established anaesthetic and known N-methyl D-aspartate (NMDA) receptor antagonist, affects the glutamatergic transmission in the brain [23]. In a preliminary study with rodents, investigators found a significant increase in glutamate in the NAcc after a ketamine injection [24]. Besides its anaesthetic properties, ketamine has antidepressant qualities [25] and shows preliminary promising results in the treatment of SUDs [26–29]: in both alcohol use disorder and CUD, less craving was observed and the number of days of abstinence was greater for individuals in the ketamine group compared to the control group. To gain a better understanding of ketamine’s mechanism of action, proton magnetic resonance spectroscopy (^1^H-MRS) provides in vivo and non-invasive insight into neurometabolism [30]. With a tailored approach, it is possible to measure glutamate levels even in small subcortical regions such as the NAcc [31]. Therefore, we will investigate if ketamine changes glutamate levels in patients with CUD in the NAcc together with its impact on the cue-induced increase of glutamatergic transmission associated with craving states. In addition, we will test if baseline levels of glutamate in the NAcc might serve as a potential biomarker predicting the clinical outcomes of the study and therefore are capable of assisting a stratified treatment approach in SUD. Furthermore, in addition to its direct effects on glutamatergic neurotransmission, ketamine is thought to increase synaptic neuroplasticity by promoting long-term potentiation (LTP) and inhibiting long-term depression (LTD) in neurons [32, 33], key substrates of learning- and memory-related synaptic plasticity typically involving the activation of NMDA and alpha-amino-3-hydroxy-5-methyl-4-isoxazolepropionic acid (AMPA) receptors. Via AMPA activation and a subsequent augmented release of brain-derived neurotrophic factor (BDNF) [34–37] and mTOR [35, 38], ketamine promotes protein synthesis, synaptogenesis, and strengthening of existing synapses [37–40]—all prerequisites of neuroplasticity. This supports the notion that ketamine opens a window of opportunity for learning and plasticity.

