#### Primary outcomes

This study primarily seeks to determine whether the interventions, namely the single ketamine infusion, the reward imagery rt-fMRI NFT, and those two interventions combined compared to the placebo conditions show a therapeutic effect by reducing the proportion of cocaine use days. The primary efficacy value is the proportion of cocaine use days between intervention groups on follow-up visit (t3). This is measured using the timeline follow back for cocaine use, which is a standardised and validated instrument to assess cocaine use [57].

In addition to the treatment outcome, the mechanism of action of the interventions is assessed. Firstly, changes in accumbal glutamate levels in the NAcc on the intervention visit I (t1) before and during the ketamine/placebo infusion and on the following intervention visit II (t2), approximately one week after the ketamine/placebo administration are measured by using ^1^H-MRS. Secondly, the mechanistic effects of the reward imagery rt-fMRI NFT are assessed by measuring its clinically relevant transfer effect, which is defined as the difference in performance on the intervention visit I (t1) and the intervention visit II (t2) measured in the percent signal change in the NFT region by using rt-fMRI.

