## Statistical methods

### Statistical methods for primary and secondary outcomes {20a}

The central hypothesis that the active treatments reduce the “proportion of cocaine use days” is tested by implementing an analysis of covariance (ANCOVA) with the between-subjects factor treatment groups (i.e. rt-fMRI NFT/placebo, rt-fMRI NFT/ketamine, sham NFT/placebo, and sham NFT/ketamine) once for each treatment (i.e. NFT and ketamine) for the follow-up visit (t3). The initial ANCOVA includes variables that potentially differ between groups at baseline as potential confounding variables, namely age, gender, substance use, and severity of dependence. To retain the simplest model, all the baseline variables that do not contribute to the outcome variable ‘proportion of cocaine use days’ are excluded from the model. Should none of the baseline variables that differ between groups contribute to the outcome variable, an analysis of variance (ANOVA) is performed. Post-hoc tests are adequately corrected for multiple comparisons.

Changes in glutamate levels in the NAcc due to the ketamine infusion on intervention visit I (t1) are analysed by applying an ANOVA for repeated measurements as not many dropouts for one of the pre-ketamine and post-ketamine glutamate assessments are expected. The main source of dropouts is expected to be of technical nature, causing insufficient data quality of the ^1^H-MRS, while dropout due to lack of compliance between the two measurements is less plausible since they take place on the same day. The ANOVA for repeated measurements includes the between-group factor treatment group (i.e. rt-fMRI NFT/placebo, rt-fMRI NFT/ketamine, sham NFT/placebo, and sham NFT/ketamine) and the within-group factor time (pre-ketamine infusion vs. post-ketamine infusion). Post-hoc test is adequately corrected for multiple comparisons. To test for sustained effects of the ketamine infusion on glutamate concentrations in the NAcc between intervention visit I (t1) and intervention visit II (t2), a multilevel analysis is applied that allows to (i) analyse multiple events in one model, (ii) include subjects with incomplete data sets, (iii) account for different time intervals between the events (7 to 14 days).

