## Discussion

This clinical study has the potential to constitute an urgently needed major advancement for the treatment of CUD by proposing a novel individualised and integrated pharmaco-psychotherapeutic intervention. This intervention is deeply rooted in the latest understanding of the neurobiological adaptations associated with CUD as derived from animal models [20, 21, 80] and clinical trials [19, 81–83]. We expect that the proposed pharmacological intervention will take preclinical molecular insights from bench to bedside and boost the development of novel pharmacotherapies for CUD and potentially other SUD by establishing glutamate signalling as a validated target for SUD therapy in humans. Our neuroimaging assay will allow for quantifying target engagement (i.e. the capacity of ketamine to restore glutamate signalling) together with its impact on substance craving and taking on an individual level, therefore paving the way for personalised treatment approaches by establishing accumbal glutamate concentration as a predictive biomarker. Moreover, allowing individuals with CUD to specifically restore the sensitivity of their maladaptive reward system to non-substance related reinforcers by means of rt-fMRI NFT assisted mental reward imagery constitutes a novel, very specific and highly individualised approach for psychotherapy of CUD and, if successful, also for other SUD. In addition, by combining pharmacologically induced neuroplasticity with rt-fMRI NFT-guided learning, we aim to boost the effect of the stand-alone interventions that are ideally suited to complement each other. Therefore, the findings from this study have the potential to foster novel treatments for other neuropsychiatric diseases (e.g. depression, posttraumatic stress disorder, anxiety disorders) as well that could benefit from synergistic effects achieved by combining rt-fMRI NFT-guided learning and pharmacologically boosted neuroplasticity.

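### The additional analysis asks whether treatment effects depend on CUD severity, affect and stress, but the correlations it names contain no comparison between arms and can confuse prognosis with effect modification

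*Protocol article*

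**What the plan says.** The section Methods for additional analyses (e.g. subgroup analyses) {20b} of the protocol article has two sentences. The first gives the aim and the method together: to learn whether effects on the primary outcome "depend on the severity of CUD, affect, and stress, the correlations between those measures are assessed". The second adds that "Post-hoc tests are adequately corrected for multiple comparisons".

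The primary outcome (Outcomes {12}) is the proportion of cocaine use days at t3, compared between groups. It is each participant's level of use and not an individual treatment effect.

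In Statistical methods for primary and secondary outcomes {20a}, severity appears only as a candidate covariate: "The initial ANCOVA includes variables that potentially differ between groups at baseline as potential confounding variables, namely age, gender, substance use, and severity of dependence". In Sequence generation {16a} it is one of the minimisation variables. No treatment-by-moderator term, stratified effect estimate or comparison of correlations between arms appears anywhere in the article.

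**The concern.** Whether an effect depends on a baseline characteristic is a question about the difference between arms: is that difference larger at one level of the characteristic than at another? A correlation between the characteristic and cocaine use days shows only that, for example, more severe participants use more. It can be strong when the treatment effect is the same for everyone, and near zero when the effect varies considerably.

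The plan already treats severity as possibly related to outcome regardless of arm, because it minimises on it and adjusts for it. That is exactly the condition under which a correlation misleads. A reader shown a significant correlation under this section's stated aim would be invited to conclude that ketamine or NFT works differently by severity, affect or stress. The correction for multiple comparisons does not help, because it does not change what a correlation estimates.

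**Working it through.** The section states no figure to reproduce, so the check is of how the named method behaves in this design.

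**Inputs from the article:** N = 120, four arms of 30, 1:1:1:1 allocation, two crossed treatments.

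**Assumptions:** standardised moderator; continuous outcome; total variance of 1 within arm in the prognostic-only case and residual variance of 1 in the modification cases; each treatment shifts the outcome by 0.5 SD; two-sided 5% tests. The within-arm moderator-outcome correlation r is not given and is varied from 0 to 0.4.

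**1. Purely prognostic moderator, pooled correlation.** The two treatment shifts add 2 × 0.5² × 0.25 = 0.125 to the outcome variance, so the pooled correlation is r/√1.125. By Fisher's z, the chance of significance is about Φ(atanh(r/√1.125) × √117 − 1.96), plus the negligible other tail when r > 0.

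| Assumed r | r/√1.125 | atanh × √117 | Correlation significant | Interaction test significant |
|---|---|---|---|---|
| 0 | 0 | 0 | 5% | about 5% |
| 0.2 | 0.189 | 2.06 | 54% | about 5–6% |
| 0.3 | 0.283 | 3.15 | 88% | about 5% |
| 0.4 | 0.377 | 4.29 | 99% | about 5% |

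Simulation of the 2×2 design agrees to within about a point (about 5/55/89/99%). The interaction column comes from simulation; the treatment effect is constant, so every rejection there is a false positive.

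**2. The same, within the ketamine-treated half only (n = 60).** Only the NFT shift remains, so the variance is 1.0625. At r = 0.3: 0.3/√1.0625 = 0.291; atanh 0.291 × √57 = 2.26; Φ(2.26 − 1.96) = 62% (simulation 63%). Restricting to one treatment does not cure the problem, because there is still no contrast.

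**3. Real modification, slopes of opposite sign that cancel.** The interaction estimate has standard error 2/√120 = 0.183. For slopes of ±0.15, ±0.25 and ±0.40 the slope difference is 0.30, 0.50 and 0.80, which is 1.64, 2.74 and 4.38 standard errors. Power is therefore about 38, 78 and 99% (simulation about 37/77/99%). The pooled correlation is significant in only about 6–7% of trials, whatever the size.

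**4. Real modification, slope in the treated only.** With slope 0 in controls and 0.3, 0.4 or 0.5 in the treated, simulation gives 35/55/72% for the pooled correlation and 36/56/76% for the interaction test. Here the correlation loses little power, but a significant result still cannot be told apart from the prognostic case in step 1.

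**The case against.** The strongest reply is that the wording is loose. The section does not say pooled, Pearson, or correlation with the t3 level. The authors may have meant change scores or correlations within arms. Comparing arm-specific correlations would address modification: by simulation, a Fisher z comparison detects 35/54/74% at treated-only slopes of 0.3/0.4/0.5, much like the interaction test. This stands to the extent that the percentages in steps 1, 3 and 4 belong to the pooled reading. It does not rescue the text, because no comparison between arms is stated under any reading.

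A reader might infer that the method will mislabel these variables and generally misses true modifiers. The article does not support that. The false-positive rate depends on r, which it does not give, and is the nominal 5% at r = 0. The loss of power is severe only when slopes oppose each other.

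A reader might also extend the point to glutamate, since the background hopes that "baseline levels of glutamate in the NAcc might serve as a potential biomarker predicting the clinical outcomes of the study" and the Discussion speaks of "establishing accumbal glutamate concentration as a predictive biomarker". Neither place names a statistical method, and the additional-analyses section does not list glutamate. Nor does the Discussion rest its hopes for personalised treatment on the severity, affect or stress correlations. Those statements are not part of this point.

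Finally, this is an additional analysis outside the stated objectives, and it leaves the primary test untouched. That limits the weight of the point but does not remove it.

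**Conclusion.** The point holds for the additional-analyses section. The question posed is effect modification, and the method named does not contain the contrast needed to answer it. This is a method stated wrongly, not a detail left to a document that is not shown.

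On the pooled reading, and for assumed prognostic correlations of 0.2 to 0.4, the procedure would flag a non-modifier in roughly 55 to 99% of trials, against about 5% for an interaction test. It can also miss modification with opposing slopes. These sizes rest on the assumed r, a continuous outcome and full recruitment of 120 with no missing data. The consequence is a risk of misinterpreting an exploratory result. The point is worth correcting, but it does not threaten the trial's main conclusion.

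**What to change.** In the additional-analyses section, replace the correlations with ketamine-by-moderator and NFT-by-moderator terms in the t3 model, labelled exploratory. Four details need stating:

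- **Coding.** The primary model is written with a four-level group factor. Code treatment as two factors for this analysis and keep the moderator's main effect in the model.
- **Moderators.** Use pre-treatment values only: severity at t0, stress at t0 and a named pre-treatment affect value. In Table 1 the affect visual analogue scale is scheduled at t1 and t2 but not at t0. One option is the first t1 reading, provided it is taken before the first NFT session.
- **Multiplicity.** Three moderators by two treatments give six interaction tests. Name the correction that the section already promises and apply it to these six.
- **Reporting.** Give interaction estimates with confidence intervals. Present any pooled correlations as prognostic associations only.

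The cost is a short rewrite and no new data. The price is precision: with a standard error near 0.18 SD per SD, a 95% interval spans about ±0.36 (1.96 × 0.183), so only large modification could be shown at N = 120.

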### Methods in analysis to handle protocol non-adherence and any statistical methods to handle missing data {20c}

The primary efficacy analysis is done using the last observation carried forward (LOCF) approach on the intention-to-treat population (ITT), i.e. all participants randomised who received ketamine treatment and reward imagery rt-fMRI NFT and had at least one assessment of efficacy 35 days post-treatment are analysed. Drop-outs before the primary efficacy assessment 35 days post-treatment are replaced. The Observed Cases (OC) approach, in which only the observed values are analysed, is used for supportive analyses.

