### Sample size {14}

Sample size was determined by power analysis (G*Power 3.1) and primarily focused on ^1^H-MRS, the most critical procedure in this project to estimate the required number of participants to detect between- and within-subject effects as well as interaction of those. Prior ^1^H-MRS studies that reported significant glutamate differences with effect sizes measured in psychiatric populations within the striatum showed effect sizes of *d* = 1.6 [76], *d* = 0.89 [12], *d* = 1.93 [77], or measured in other brain regions in tobacco use disorder *d* = 1.03 [78]. Thus, assuming a conservative effect size of *d* = 0.80, an α-error probability of 5%, and a conservative power estimation of 80%, a total sample size of 21 individuals with CUD per group (total sample of 84) would be required to detect a significant group effect between experimental and control groups. Again, assuming an effect size of *d* = 0.80 (*f* = 0.40, respectively) for within-subject comparisons before and after intervention, an α-error probability of 5%, and a conservative power estimation of 80%, indicates that a total number of 111 subjects would be necessary to detect a significant within-factor effect in an ANCOVA model. To account for potential dropout, we will recruit in total 120 participants.

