## Data collection and management

### Plans for assessment and collection of outcomes {18a}

The study team monitors data in real time to ensure complete data collection for all participants, including those who discontinue treatment. Relevant data from the participant, such as eligibility criteria, demographics, height, weight, vitals, MINI [79], concomitant medications, interview for psychotropic drug consumption, and different questionnaires (see specific information in Table 1) are entered directly by the participant or investigator into the data management system at each visit. Additionally, any data that cannot directly be entered into the system is manually added by trained study personnel and verified through a double-check process. The investigators must maintain source documents for each participant in the study, consisting of demographic information, medical and psychological screening, for example, ECG assessments, laboratory tests, and the original signed informed consent form. All original paper–pencil based data and source data documents are stored in a physical participant folder, and a copy is stored electronically on the password-protected study servers provided by the Psychiatric University Hospital Zurich. Also, the collected ^1^H-MRS and reward imagery rt-fMRI NFT data for each visit are stored on the study server. Data which is collected with the EMA application is stored in an instance of Google’s cloud-based Firestore database in an anonymised fashion [71]. In addition, a backup copy of the EMA data is saved on the study server.

For collecting the data, only standardised questionnaires and tested procedures are used.

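### The population called intention-to-treat requires treatment received and a day-35 assessment, and earlier drop-outs are replaced, so the primary comparison is not protected against informative loss

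*Protocol article*

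**What the plan says.** Section {20c} of the protocol article sets four rules for the primary efficacy analysis.

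- **Population.** The set labelled intention-to-treat is "all participants randomised who received ketamine treatment and reward imagery rt-fMRI NFT and had at least one assessment of efficacy" at 35 days after treatment.
- **Missing values.** Last observation carried forward (LOCF) is applied to that set.
- **Replacement.** "Drop-outs before the primary efficacy assessment 35 days post-treatment are replaced".
- **Support.** "The Observed Cases (OC) approach, in which only the observed values are analysed, is used for supportive analyses".

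Four other places bear on this. Under Primary outcomes {12}, the primary efficacy value is the proportion of cocaine use days at t3, from the timeline follow back. Table 1 puts t3 at day 35 to 49, and randomisation at t0, 10 to 84 days before the infusion visit t1. Sample size {14} goes from 111 to 120: "To account for potential dropout, we will recruit in total 120 participants". Section {18a} says that the team will "ensure complete data collection for all participants, including those who discontinue treatment".

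**The concern.** An intention-to-treat set is fixed by randomisation alone. This one adds two conditions that are met only later: treatment was received, and the day-35 assessment took place. Whoever is lost before that assessment is outside the set on its natural reading, and a new recruit takes the place.

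Both routes to bias are plausible here. Loss may be related to arm: the comparator is saline, and section {11a} prepares participants for challenging experiences during the infusion. Loss may also be related to outcome, if people who return to heavier use are harder to retain. If both hold, the arms being compared are no longer the arms that were randomised. Replacement fills the gaps and makes the attrition less visible, and the planned supportive analysis could not reveal it. A reader who sees the result reported as intention-to-treat would assume a protection that the set does not give.

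**Working it through.** **1. Entry conditions against the endpoint.** The set requires an efficacy assessment 35 days after treatment (section {20c}). The primary endpoint is measured at t3 (Primary outcomes {12}), and the t3 window opens at day 35 (Table 1). On the natural reading, membership therefore requires the t3 value itself. LOCF then has no missing t3 value to fill, and observed cases are essentially the same people as the primary set.

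**2. A looser reading.** If the condition means at least one assessment *within* 35 days, a participant with only a t2 timeline follow back would qualify and the t2 value could be carried forward. But that participant dropped out before the primary assessment, and the next sentence replaces such people. Carrying the value forward and replacing the person are two different treatments of the same case. The section does not say which applies.

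**3. The plan's own allowance.** No drop-out rate is stated. The step from 111 to 120 implies 1 − 111/120 = 7.5%.

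**4. Possible size of the bias.** All inputs are assumed, because the documents give none. There is no true effect. A fraction r of each arm relapses to a use-day proportion of 0.65 and the rest are at 0.35. Relapsers drop out with probability q, which is 0.75 under placebo and 0.25 under ketamine; nobody else drops out.

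Mean among those with t3 = [(1 − r) × 0.35 + r(1 − q) × 0.65] / [(1 − r) + r(1 − q)]

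- r = 0.2, placebo: (0.28 + 0.0325)/0.85 = 0.368
- r = 0.2, ketamine: (0.28 + 0.0975)/0.95 = 0.397
- r = 0.3, placebo: (0.245 + 0.04875)/0.775 = 0.379
- r = 0.3, ketamine: (0.245 + 0.14625)/0.925 = 0.423

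The mean over all randomised is 0.410 (r = 0.2) or 0.440 (r = 0.3) in both arms. The false difference against ketamine is 0.030 or 0.044. It changes sign if the drop-out pattern is reversed. Overall loss in these scenarios is rq: 15% v 5%, or 22.5% v 7.5%.

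**5. On a standardised scale.** This is a simulation, again under assumed inputs: no true effect, 60 v 60 participants with t3 after replacement, correlation 0.5 between cocaine use and propensity to drop out, two-sided 5% test.

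| Drop-out, active v control | Bias (SD) | Type I error |
|---|---|---|
| 10% v 10% | 0.00 | 5.0% |
| 10% v 20% | 0.08 | 7.2% |
| 10% v 30% | 0.15 | 13.4% |
| 5% v 25% | 0.16 | 14.6% |

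Equal loss gives no bias in this model.

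**6. Would counting missing days as use days be a safe check?** Use the step 4 scenarios and set each drop-out to 1.

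- r = 0.2: placebo 0.3125 + 0.15 = 0.4625; ketamine 0.3775 + 0.05 = 0.4275
- r = 0.3: placebo 0.29375 + 0.225 = 0.519; ketamine 0.39125 + 0.075 = 0.466

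This is a false benefit *for* ketamine of 0.035 or 0.053, larger than the bias it was meant to guard against.

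**7. Numbers of people.** At assumed loss of 5%, 10%, 20% or 30%, obtaining 120 participants with t3 by replacement takes 120/(1 − loss), rounded up, less 120: 7, 14, 30 or 52 extra randomised people. Without replacement, 120 × (1 − loss) gives 114, 108, 96 or 84 observed t3 values.

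**The case against.** Several parts of the case against this criticism stand.

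- **The text is ambiguous.** The phrase about at least one assessment fits poorly with a single visit, and section {20c} says replaced, not deleted. It cannot be said with certainty that LOCF never operates. What stands is that the natural reading makes it empty and the looser one collides with the replacement sentence.
- **Sample size {14}.** A reader might infer that replacement contradicts the allowance from 111 to 120. The documents do not establish that. The sizing is primarily for spectroscopy, and section {20a} expects losses in the same-day glutamate comparison to be mainly technical. An allowance for unusable spectra can coexist with replacement; the two are uncoordinated.
- **Section {18a}.** Nor is there a strict contradiction with collecting data after discontinuation. Someone who had the infusion and the t1 training, missed t2 and attended t3 could still be in the set.
- **The word ketamine.** Read literally, the definition excludes both placebo arms. The intervention sections consistently describe ketamine/placebo and real/sham training, so this is loose wording to correct and nothing more.
- **Loss before t1.** It occurs under blinding and before any treatment, so it is unlikely to depend on arm. The concern is loss after the infusion.

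None of this rescues the label. Two post-randomisation conditions still define the primary set.

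**Conclusion.** The point holds. The primary efficacy set is wrongly called intention-to-treat, and its missing-data rules are either empty or in conflict with replacement, depending on the reading.

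A reader might infer that randomisation is destroyed or that the result will be biased. The documents do not support that. Bias requires loss related to both arm and cocaine use, and no drop-out rates by arm are given. Size and direction are therefore unknown. The figures of about 0.03 to 0.04 in use-day proportion, and type I error of 7.2% to 14.6% under unequal loss, rest wholly on assumed scenarios. The use-day figures are not set against a target difference or standard deviation, so they show that an effect is possible and do not measure its importance.

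The finding that rests on the text alone is that the primary analysis is exposed to this bias and the planned supportive analysis could not detect it.

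**What to change.** 1. Define the primary population as all randomised participants, analysed as allocated. Where treatment receipt is described, write ketamine/placebo and NFT/sham.
2. Keep drop-outs in the analysis and do not substitute replacements for them.
3. Replace LOCF with a mixed model or multiple imputation under missing-at-random, using the timeline follow back from t0 to t2 and t4. Section {20a} already plans a multilevel analysis for glutamate partly because it admits incomplete data. Missing-at-random removes the bias only as far as the observed follow-back data capture relapse.
4. Because the instrument is retrospective, ask at t4 about days missed at t3. This helps only for participants who can still be reached.
5. Add a missing-not-at-random sensitivity analysis, delta-adjusted or tipping-point, in which the assumption varies by arm. Do not rely on a single rule that missing equals use; it can favour ketamine when placebo loses more.
6. Keep the present set as a supportive analysis, labelled as completers.

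**Cost.** The estimate may be less favourable. With 120 randomised and no replacement, loss above 7.5% leaves fewer than 111 observed t3 values (96 at an assumed 20%). A protocol amendment is needed, and section {25} requires ethics approval for substantial changes. The article reports recruitment as ongoing with three participants finished at submission, so the amendment could be made before unblinding.
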